## Abstract

Virtual reality (VR) technology is often referred to as the ‘ultimate empathy machine’ due to its capability to immerse users in alternate perspectives and environments beyond their immediate physical reality. In this study, participants will be immersed in 3-dimensional 360° VR videos where actors express different emotions (sadness, happiness, anger, and anxiousness). The primary objective is to investigate the potential relationship between participants’ empathy levels and the changes in their physiological attributes. The empathy levels will be self-reported with questionnaires, and physiological attributes will be measured using different sensors. The main outcome of the study will be a machine learning model to predict a person’s empathy level based on their physiological responses while watching VR videos. Despite the existence of established methodologies and metrics in research and clinical domains, our aim is to contribute to addressing the gap of a universally accepted “gold standard” for assessing empathy. Additionally, we expect to deepen our understanding of the relationship between different emotions and psychological attributes, gender differences in empathy, and the impact of narrative context on empathic responses.

## Introduction

Empathy is a multifaceted and complex topic that has captured the interest of researchers across many different fields, including psychology, neuroscience, philosophy, sociology, and anthropology. Although there is no widely accepted definition of empathy, there is a consensus regarding its multidimensional nature. For instance, one of the most used theoretical models is the one that conceives empathy as encompassing a cognitive component (i.e., the capacity for understanding another person’s experience and perspective) and an emotional component (i.e., the ability to experience the emotional state of another person) [1, 2]. For the purpose of our research, we regard empathy as the ability or tendency to construct a working model of the emotional states of others and be sensitive to and experience other people’s feelings, while maintaining the awareness of the distinction between self and other [3].

Understanding the reasons why empathy is worth investigating can shed light on its significance in different domains. Here are some key points:

Importance of empathy in social relationships and cross-cultural differences in empathy: Empathy plays a crucial role in social interactions, enabling individuals to understand and experience the emotions of others. Moreover, cultural variations in empathy emphasize the diverse importance placed on empathy across different cultures. Research on empathy not only reveals its impact on forming and maintaining relationships, resolving conflicts, and fostering interpersonal connections but also provides insights into cross-cultural differences, helping us understand the factors that shape these variations and their implications for intercultural communication and understanding [4–6].Prosocial behavior and altruism: Empathy has a strong link to prosocial behavior, such as helping, volunteering, and displaying altruistic acts. Investigating empathy can reveal how it influences individuals’ willingness to support others and contribute to the well-being of society [7, 8].Mental health implications: Empathy deficits are observed in certain psychiatric disorders, including autism spectrum disorder, borderline personality disorder, and antisocial personality disorder. Research on empathy aids in understanding the underlying mechanisms of these deficits, potentially leading to improved diagnostic tools and therapeutic interventions [5].Technological applications: As virtual reality and artificial intelligence continue to gain prominence, there is an increasing focus on developing technologies that have the ability to stimulate empathy. Empathy-based technologies are those that leverage the understanding of human empathy to enhance user experiences, communication, and interactions. They utilize techniques and features that evoke or facilitate empathic responses from users. For example, in the field of VR, empathy-based technologies may involve creating virtual scenarios that allow individuals to embody different perspectives, emotionally connect with characters, or experience situations that elicit empathy towards others [9].

Often, empathy and prosocial behavior are mistaken as the same concept. They are related, but differ in their nature and manifestation. As we mentioned before, empathy involves understanding and experiencing others’ emotions and experiences, fostering compassion and connection. Prosocial behavior, on the other hand, comprises actions aimed at benefiting others, such as kindness, cooperation, and altruism. While empathy can lead to prosocial behavior, they are distinct entities. Empathy serves as a cognitive and motivational precursor to prosocial actions, as it fosters a sense of responsibility and compassion, motivating individuals to help and support others [4, 7, 10–13].

While there is no universally agreed-upon “golden standard” for measuring empathy [14], several established methods and measures are commonly used in research and clinical settings, including self-report questionnaires, behavioral observation, psychophysiological measures and performance tasks.

Self-report questionnaires: Self-report questionnaires involve participants answering a series of questions about their thoughts, feelings, and behaviors related to empathy. These questionnaires typically assess self-perceived empathy levels and provide insights into individuals’ subjective experiences. However, one limitation is that self-report measures rely on participants’ self-perceptions and may be subject to response biases, such as social desirability or inaccurate self-assessment [15, 16].Performance tasks: Performance tasks assess individuals’ empathic abilities through specific tasks or simulations designed to elicit empathic responses. These tasks often involve scenarios where participants must infer and understand others’ emotions or engage in perspective-taking. Performance tasks can provide more ecologically valid measures of empathy and overcome some limitations of self-report measures. Despite the need for careful design and the potential influence of factors such as task demands and individual cognitive abilities, the primary limitation of this method is its inability to measure the emotional dimension of empathy, potentially yielding lower levels of genuine empathic understanding. It is worth noting that individuals lacking empathy altogether may still possess effective advocacy skills [4, 17].Behavioral observation: Behavioral observation involves directly observing and recording individuals’ empathic behaviors in real-world or controlled settings, without specific tasks designed to elicit empathy. Researchers use standardized coding schemes to quantify specific empathic behaviors, such as facial expressions, vocal tone, or prosocial actions. While behavioral observation provides objective data on actual empathic behaviors, it may be time-consuming, and the presence of observers might influence participants’ behavior, leading to potential reactivity biases [18]. Furthermore, it is important to note that this method primarily measures behavior rather than the emotional dimension of empathy.Psychophysiological measures: Psychophysiological measures assess physiological responses linked to empathy, like heart rate changes, skin conductance, and brain activity. These measures offer objective data on participants’ physical reactions during empathic experiences. There are studies [19, 20] examining psychophysiological measures to understand empathy’s neural and physiological mechanisms. They used techniques like fMRI and EEG to explore brain activity during tasks involving empathetic responses. While not predicting empathy directly, their research has enhanced the understanding of neural processes in empathetic experiences, elucidating the role of mirror neurons and brain areas responsible for emotional processing in contributing to this comprehension. However, psychophysiological measures also have their limitations: sensitivity to non-empathetic factors, potential inter-individual variability, and equipment constraints.

The choice of measurement depends on the specific research objectives, population under study, and the dimensions of empathy being assessed. It is important to consider that each measurement method has its strengths and limitations. To combat the limitations, researchers often use multiple measures in combination to capture the different facets of empathy comprehensively. This increases the complexity of measuring empathy, even though some individual measures are already complex and time consuming. Ideally we would like a measure of empathy that is reasonably objective and can be while applied during arbitrary tasks (i.e., it does not require the performance of a specific task). Psychophysiological measures satisfy these requirements best, the precise connection between these measures and empathy remains an open question. Our study aims to aims to bridge this gap by developing a powerful machine learning model that directly measures empathy based on physiological signals, offering a novel and more targeted perspective on empathetic responses.

VR is a computer-generated technology that simulates a realistic environment, allowing users to immerse themselves and interact with the virtual world. By wearing a VR headset and sometimes using accompanying peripherals, users can experience a sense of presence and engage with virtual objects and environments as if they were physically present, providing an immersive and often interactive experience [21, 22]. VR has shown promise in evoking empathy and emotional engagement across various domains and has been explored as a valuable tool for empathy training [23, 24]. Thereby, numerous scientific papers have put forth assertions that VR has the potential to evoke empathic behavior, labeling VR technology as ‘the ultimate empathy machine’ [25]. Some of the key points why VR is called ‘the ultimate empathy machine’ are: 1) immersive and embodied experience: VR can create a sense of presence and immersion, allowing users to embody different perspectives and experiences. This immersive quality has the potential to enhance empathy by enabling individuals to see and feel situations from another person’s point of view [26]; 2) perspective-taking and emotional engagement: VR experiences can simulate realistic scenarios that elicit emotional responses and engage users in perspective-taking. By experiencing the world through someone else’s eyes, individuals may develop a deeper understanding of others’ feelings and experiences [27]. There is a study that demonstrated VR has the potential to enhance emotional well-being and evoke empathy among the elderly. It exposed them to emotionally engaging content, such as storytelling elements and immersive environments depicting scenarios relevant to their interests, like virtual tours of nostalgic places. Additionally, it facilitated simulated social interactions with family members or peers, designed to evoke empathy and emotional engagement [28]; 3) empathy training and perspective shift: In domains like healthcare, education, and diversity training, VR-based interventions are designed to enhance empathic abilities. By immersing individuals in lifelike scenarios, VR challenges their preconceptions and encourages perspective-taking. The highly realistic and interactive nature of VR experiences allows participants to gain deeper insights into the emotions and experiences of others, making it a powerful tool for empathy training [24]. There is a study where VR emerges as a powerful tool for cultivating empathy, particularly in addressing sensitive topics like racism, inequity, and climate change within the medical field. Through immersive VR experiences, participants engage in transformative conversations, enhancing their capacity for empathy and understanding in diverse healthcare contexts [29]. Additionally, there is a study that investigates the impact of dementia VR-based training with peer support on home care workers’ understanding and empathy towards dementia patients. The researchers assessed the effects of a comprehensive training program on dementia knowledge, attitudes, competence, and empathy among home care workers through a cluster randomized controlled trial and the results indicate significant improvements in these domains among participants who received the VR-based training compared to the control group, suggesting the efficacy of innovative training approaches in enhancing dementia care skills among home care workers [30]; 4) ethical considerations: While VR can foster empathy, its use must be approached with ethical considerations. As an ‘ultimate empathy machine,’ VR has the potential to evoke strong emotional responses in users. Thus, responsible design is essential to ensure that VR experiences respect the dignity and privacy of individuals involved. Moreover, careful management of emotional impact is crucial to prevent any potential negative consequences on participants’ well-being. Striking a balance between creating immersive empathic experiences and safeguarding participants’ emotional welfare is imperative in utilizing VR as an empathy-enhancing tool [31].

The aim of this study is to research how the empathy of the participants is related to changes in their physiological attributes measured by different sensors (inertial measurement unit, photoplethysmogram, eye tracking, electromyography (EMG), electrodermal activity, 3-axis accelerometer). Using a VR headset, the participants are going to be immersed in 3-dimensional 360° videos of actors who express different emotions (sadness, happiness, anger and anxiousness). They will report their experience of empathy through short questionnaires. Based on their sensor and questionnaires data, a machine learning model will be developed that will predict a person’s score on an empathy questionnaire based on their physiological arousal while watching VR videos.

The development of a stable and accurate model for predicting people’s level of empathy would offer several benefits as: 1) personalized interventions and early intervention/prevention: individuals’ empathy levels could be assessed in various contexts, such as healthcare, education, and counseling, allowing for tailored interventions and treatments to enhance empathic abilities. Additionally, identifying individuals with lower empathy levels early on could enable targeted interventions and preventive measures, particularly in fields where empathy is crucial, such as healthcare and interpersonal relationships, helping to avert potential negative outcomes or conflicts. 2) selection and training: the model could assist in selecting individuals for roles that require high levels of empathy, such as counseling, customer service, or leadership positions. It could also guide training programs by identifying areas where individuals may benefit from additional support or development; 3) research and understanding: a reliable model for predicting empathy levels could contribute to research efforts in understanding empathy and its role in various aspects of human behavior, relationships, and societal dynamics. It could provide insights into factors influencing empathy and help identify patterns and trends across different populations; 4) entertainment and interactive media: by tailoring content to users’ empathic tendencies, creators can offer more emotionally engaging experiences in video games, interactive narratives, and recommend personalized media choices, enhancing emotional resonance and user satisfaction; 5) personal growth and self-awareness: individuals who have access to information about their own empathy levels could gain a better understanding of their strengths and areas for improvement. This self-awareness could foster personal growth and encourage individuals to develop and cultivate empathy as a valuable skill. Overall, a stable and accurate model for predicting people’s level of empathy could have significant implications for personalized interventions, early intervention and prevention, selection and training processes, research advancements, entertainment and interactive media, and individual self-awareness and growth in fostering empathy [3, 5, 32, 33].

## Materials and methods

### Empathy elicitation using VR

Based on the narrative review on the use of VR for eliciting empathy [1], we have decided to immerse participants in 360º and three-dimensional (3D) virtual environment due to VR’s efficacy in eliciting empathic responses. Our choice of a 360º immersive setting is substantiated by comparative analyses demonstrating that it is equally or more effective at eliciting empathy compared to other approaches such as two-dimensional video/film [1, 34, 35], curriculum contents like workshops [36] or e-course materials [37], narrative-based perspective-taking exercises [9, 38], and text-based information [9, 35]. This effectiveness is observed immediately or with a lasting positive impact. Additionally, our decision to utilize a 3D level of immersion aligns with the findings of the review [1], which highlight the superior effectiveness of 3D immersion over two-dimensional.

During the VR experience, participants will adopt a first-person perspective, allowing them to observe the actors expressing emotions directly in front of them. This approach was chosen because research suggests that a first-person perspective is more effective than a third-person perspective, where the participant merely observes events happening among others [39, 40].

We decided on videos where actors genuinely express four distinct emotions (happiness, sadness, anger, and anxiousness), without any accompanying content, words, or explanations. This decision was driven by the aim to minimize the potential influence of content on evoking emotions, as it would complicate the differentiation between empathy and emotions triggered by the content itself [31]. Moreover, individuals may exhibit distinct empathic responses to different emotional valences, which is why we have included four different emotions in the study [41]. However, recognizing that some participants may find it more impactful to understand the reasons behind the emotions, we also developed a narrative version of the VR session. This version includes an emotional narrative conveyed through audio, followed by a corresponding video of the actor expressing the emotion (50—120 seconds). In order to ensure a gender-balanced distribution, we have recorded videos featuring two male and two female actors. Furthermore, we have created two separate versions of the narrative. Each version is composed of four distinct parts, with each part corresponding to one of the expressed emotions (Fig 1). The narratives uphold a thematic consistency concerning childhood abuse, abandonment, and mother-child relationships.

**Fig 1 pone.0307385.g001:**
[figure not shown]
Top to down: (left) Actor one (Dave in the narrative) expressing anger and (right) Actor two (Jake in the narrative) expressing happiness; (left) Actress one (Anna) expressing sadness and (right) Actress two (Leah) expressing anxiousness.

In the first narrative, we follow the story of two sisters, Leah and Anna, whose childhood was marred by fear and violence due to their abusive father, leading to their mother’s departure. The sisters carry the painful memory of silently watching their mother pack her bags, eventually ending up in an orphanage. Leah finds solace and success in her academic pursuits, securing a scholarship to study abroad. However, a recent encounter with their mother reignites Anna’s anger as she confronts her about the past, only to be met with a lack of remorse. This encounter leaves Anna questioning the concept of family and regretting their decision to reconnect (see S1 Appendix). There is also one more version written for males with the same storyline (see S2 Appendix).

The second narrative delves into the experiences of two brothers, Jake and Dave. Jake learns of their mother’s stroke after three years of no contact, and he is overwhelmed by sadness. He is deeply hurt by her blame and refusal to see them. Meanwhile, Dave grapples with anxiousness, burdened by their dysfunctional family dynamics and regretting his incomplete education. Although he desires a job change, he hesitates to seek assistance, considering the responsibilities his brother already faces. On a positive note, Jake experiences happiness and anticipation as he and his girlfriend expect a baby, triumphing over their concerns about conception. Lastly, Dave expresses his anger towards their parents for the detrimental impact on his life (S3 Appendix). There is also one more version written for females with the same storyline (see S4 Appendix).

### VR sessions

The sessions, conducted with and without narratives, are structured in the following manner:

With narratives:
In preparation for the session, the participants will be requested to fill out questionnaires pertaining to personal information, including age, gender, health status, proficiency in the Slovenian language, prior experiences with VR, employment or study status, field of work or study, and educational background. This questionnaire, developed by our team, is provided in S5 Appendix. Additionally, participants will be asked to complete the Questionnaire of Cognitive and Affective Empathy (QCAE) [3] to assess their trait empathy. Trait empathy represents the individual’s innate capacity for empathetic behavior and is closely linked to personal characteristics [42].The first step of the VR session is calibration. To calibrate the baseline, participants will be asked to relax, breathe normally, and avoid facial expressions and head movements during a 2-minute recording. They will later be prompted to perform several voluntary facial expressions. The data recorded during these voluntary facial expressions will inform the subject-specific normalization of EMG signals, following the approach suggested in certain studies [43–45].Following the calibration process, participants will be exposed to a 2-minute forest video. Its purpose is to establish a baseline, reflecting the participants’ relaxed state. The forest video utilized in this study was an existing video titled ‘The Amsterdam Forest in Springtime,’ sourced from YouTube.Subsequently, the main segment of the session entails the four sets of narrative-video pairs. Each pair consists of the emotional narrative read by the corresponding actor, followed by the video portraying the actor expressing the specific emotion. The emotions portrayed in these pairs include anger, sadness, happiness, and anxiousness. The duration of each narrative-video combination ranges from 2 to 3 minutes. The participants will be instructed to empathize with the individuals in the video recordings.Following the observation of each narrative-video pair, participants will provide brief feedback on their current empathic state. They will do so by answering three out of the four different items that measure affective empathy from the 12-item State Empathy Scale developed by Lijiang Shen, based on the Interpersonal Reactivity Index (IRI). The selection of these three questions specifically is made because factor analysis requires at least three indicators or items per factor. We have excluded the first item in this scale as it appears to assess the quality of the actor’s performance rather than empathy. Therefore, we specifically utilized the 2nd, 3rd, and 4th items before moving on to the next pair [46]. State empathy refers to the temporary affective response evoked in specific situations [47]. This procedure will be repeated four times, with each iteration featuring a distinct emotion. The duration of each empathic state report is expected to be up to 30 seconds.In addition to the state empathy questions, participants will be requested to provide brief feedback on their current arousal and valence states using the arousal and valence statements from the self-assessment manikin (SAM) affective rating system [48]. This inclusion of arousal and valence measures alongside state empathy is crucial because it offers a more comprehensive insight into emotional experiences during VR sessions. Arousal and valence are fundamental components of emotional responses and are often intertwined with empathy [49].After the participants provided brief feedback on their current arousal and valence states, we included one item to assess personal distress, specifically question number 17 from the personal distress items based on the IRI [15].The final segment of the session involves a roller coaster video titled ‘Official 360 POV—Yukon Striker—Canada’s Wonderland’, which was sourced from YouTube. This video, as a control measure were implemented, to address potential confounding variables, particularly to differentiate between non-empathic psychological arousal and the empathic arousal expected from the main video. While the primary response stimuli consisted of videos designed to evoke empathic physiological arousal, a control stimulus, namely a roller coaster video, was incorporated to induce non-empathic arousal. We believe that this strategic control will facilitate the differentiation between empathic and non-empathic responses, enhancing the validity and reliability of the study’s findings. One of our experiments aims to examine the differences in physiological responses between empathically stimulating content and non-empathic, arousal-inducing content, such as the roller coaster video.The session’s final segment is followed by the arousal and valence statements from the SAM affective rating system [48], with the aim of comparing the intensity of arousal and valence after the roller coaster video and arousal, valence and empathic states following each pair of narrative-video.At the conclusion of the session, we will administer a presence questionnaire adapted from the Bongiovi Report [50]. The questionnaire has been modified to include questions from the presence section, as well as an additional inquiry regarding any challenges encountered by participants that may have hindered their VR experience (refer to S6 Appendix).Without narratives:
The overall procedure remains the same as with narratives, with the exception of the main segment where the four emotions will be portrayed by all four actors without accompanying narratives. The actors will exhibit a gradual progression into each emotion, reaching its peak intensity before returning to a neutral state. This session is suitable for participants of all linguistic backgrounds.

Taking into account recommendations for minimizing VR sickness and potential health concerns, the duration of the videos, including the calibration step, will be around 20 minutes [51]. Each participant will be assigned one of five available versions for viewing: actresses with the first narrative version, actresses with the second narrative version, actors with the first narrative version, actors with the second narrative version, or the version without narrative.

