### Data analysis

In order to process the collected data effectively, several steps will be taken. Firstly, the derived features obtained from each module of the Emteq Emotion AI Engine, as well as the features from the Empatica E4, will be combined by concatenating the data files. The epoch timestamps will then be converted to human-readable date and time formats, and the output labels will be populated based on the scores from the empathy questionnaires. The classification task will involve multi-label classification, with the affective component of trait empathy and state empathy serving as the labels of interest.

If a variable has a modest amount of missing values, imputation will be used. Otherwise, if the amount is substantial, the corresponding data will be dropped. The derived features are provided by different devices with data updated at different intervals, ranging from 10 seconds to 500 milliseconds, resulting in varying data frequencies. Undersampling or oversampling will be used to handle the high or the low frequency of the derived features accordingly, and they will be aligned at a consistent interval. Regarding the variables, while some are ready to be used, as the derived features are, from others, such as the raw sensor data, we will extract features.

The research aims to address several key questions. Firstly, it seeks to explore the connection between physiological attributes and empathy. For this purpose we will use multiple standard machine learning classifiers to develop prediction models, with different parameters tested to optimize performance. The predictive models will be developed based on the descriptive space consisting of physiological data from the sensors and data from the questionnaires. Additionally, personalized models will be explored to enhance predictions. Personalized feature values will be utilized, employing normalization techniques by calculating the ratio between the parameter value and the average value for each participant over the entire viewing period. If the initial results prove unsatisfactory, deep learning techniques will be applied directly to the raw sensor data, bypassing the use of the derived features provided by Emteq. Furthermore, we will explore deep learning approaches using the derived features, allowing us to consider both options.

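### In the four narrative versions one state-empathy rating covers story and clip together, so a model pooled over versions can gain accuracy by detecting who heard a story

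*Protocol article*

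**What the plan says.** All references are to the protocol article.

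- **Aim on content (Empathy elicitation using VR).** Wordless clips were chosen to limit the influence of content, "as it would complicate the differentiation between empathy and emotions triggered by the content itself". The same paragraph then adds a narrative version on purpose, because some participants may respond more when they know the reason for the emotion.
- **Versions (VR sessions).** "Each participant will be assigned one of five available versions for viewing": four carry a narrative and one does not.
- **Structure of a narrative segment (VR sessions).** "Each pair consists of the emotional narrative read by the corresponding actor, followed by the video portraying the actor expressing the specific emotion".
- **Rating (VR sessions).** "Following the observation of each narrative-video pair, participants will provide brief feedback on their current empathic state". Three affective items are answered once per emotion. No rating between story and clip is described.
- **Labels (Data analysis).** Sensor features are aligned at a common interval and "the output labels will be populated based on the scores from the empathy questionnaires". The two labels are the affective part of trait empathy and state empathy.
- **Expected effect of narrative (Data analysis).** A t-test will check whether knowing the story beforehand enhances empathic response, and earlier research is cited in that direction.

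**The concern.** The article's own reason for wordless clips is that content makes empathy hard to tell from emotion evoked by that content. In four of five versions the state rating follows a story about abuse and abandonment as well as the clip. One number then stands for both.

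This matters most when versions are pooled. If narrative raises the state score, as the article expects, and listening to a story also shifts heart rate, skin conductance or facial muscle activity, then narrative exposure is related to both the label and the features. A classifier trained across versions can then do well partly by recognising which session it is looking at. Its performance would be read as evidence that physiology tracks empathy. The Discussion names a standard for measuring empathy as the primary outcome, and the Introduction suggests uses such as selecting people for roles, so this reading carries weight.

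**Working it through.** The article gives no figure on this point to reproduce. Its sample of about 100 is justified by precedent.

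**1. Which label is exposed.** Trait empathy (QCAE) is completed in preparation for the session, before any stimulus, so the story cannot affect it. State empathy is rated after the pair, so it is exposed. One of the two labels is concerned.

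**2. How much of the rated period is story.** Inputs: "The duration of each narrative-video combination ranges from 2 to 3 minutes", that is 120 to 180 s; and "followed by a corresponding video of the actor expressing the emotion (50—120 seconds", read here as the length of the clip. Narration = pair − clip.

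| Pair (s) | Clip (s) | Narration (s) | Share of pair |
|---|---|---|---|
| 120 | 120 | 0 | 0% |
| 180 | 120 | 60 | 33% |
| 150 (mid) | 85 (mid) | 65 | 43% |
| 120 | 50 | 70 | 58% |
| 180 | 50 | 130 | 72% |

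The range is 0% to 72%. Both ends combine extremes and neither is typical. Share of time is not a measure of bias; it shows only that the story is usually a substantial part of what precedes the rating.

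**3. How many participants.** 4/5 = 80% of versions. The split of participants is not stated; equal allocation of 100 (assumed) gives 80 narrative and 20 no-narrative.

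**4. How much a pooled model could gain (illustration).** Let narrative shift the state score by d within-group standard deviations, and let p be the narrative share. A feature that did nothing but identify narrative exposure would explain p(1−p)d² / [1 + p(1−p)d²] of the pooled score variance. With p = 0.8:
- d = 0.5: 0.16 × 0.25 = 0.04; 0.04/1.04 = 3.8%.
- d = 0.8: 0.16 × 0.64 = 0.1024; 0.1024/1.1024 = 9.3%.

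The values of d are assumptions. The shortcut is modest, but it would be counted as prediction of empathy.

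**5. Whether the planned t-test settles it.** Take N = 100 and two-sided alpha 0.05 (assumed), with SE of d = √(1/n₁ + 1/n₂).
- 80:20 split: SE = 0.25. Power at d = 0.5 is Φ(0.5/0.25 − 1.96) = 0.52. Detectable d at 80% power is 2.80 × 0.25 = 0.70.
- 50:50 split: SE = 0.20. Power at d = 0.5 is 0.71. Detectable d is 0.56.

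The test compares group means. Whatever its result, it does not remove story response from an individual's label or version from the model.

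**6. What the modelling text fixes.** The predictors are sensor and questionnaire data, and version is not mentioned. The only time window named is the whole viewing period, used as the denominator for personalised features; in narrative versions that period includes narration.

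**The case against.** There is a good case on the other side, and much of it stands.

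- **A reader might infer that the plan breaks its own rule.** It does not. It states an aim to minimise content, not a requirement to exclude it, and it makes the narrative exception openly and with a reason.
- **A reader might infer that the model's labels as a whole are contaminated.** Only the state label is exposed.
- **A reader might infer that rows recorded during narration, or while the actor is neutral, are given the empathy label.** The article does not say so. It does not fix the unit of analysis or the window, and it speaks of responses while watching the videos. The course of building up and "reaching its peak intensity before returning to a neutral state" is described only for the version without narrative.
- **A reader might infer that story response is not empathy.** The actor reads the story, and participants are told to empathise with the people shown and to report empathy towards the actors. Response to the story may be partly empathy; the design cannot say how much. That instruction also means a new rating instruction would add little.
- **Safeguards exist.** There are arousal and valence ratings, a personal-distress item, a roller coaster control, a no-narrative version, the t-test, and storyline influence stated as a limitation. None of them separates story from expression within one rating. The roller coaster represents non-empathic arousal rather than emotion evoked by a story, and the no-narrative version helps the model only if results are shown by version.
- **A condensed article may leave windows and strata to a fuller plan.** That is fair as to silence. The timing of the rating, however, is fixed here and cannot be undone after data collection.

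**Conclusion.** The concern holds in a limited form. In the narrative versions the state label mixes response to the story with response to the expression, and a model pooled over versions can gain apparent accuracy from narrative exposure. The trait label is unaffected.

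The size is uncertain. Narration is 0% to 72% of the pair, about 43% at mid-range, if the bracketed duration is the clip's. The 80% of participants rests on equal allocation. The gain from detecting version depends on a narrative effect that the article expects but does not quantify, and on the story altering the measured physiology, which is plausible but not shown.

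The documents do not support saying that the model measures story response instead of empathy. They support saying that a pooled result could not tell the two apart. This is a worthwhile and inexpensive improvement, not a fatal flaw.

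**What to change.** In the Data analysis section:

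1. Pair the state label with sensor features from the expression clip only, leaving out narration and rating periods.
2. Report state-label model performance separately for narrative and no-narrative participants (or within version), beside the pooled figure, and limit the empathy claim to what holds within version.
3. If a model trained on narrative participants is tried on no-narrative participants, call it exploratory. That group is about 20 people under equal allocation of 100, and its version also differs in showing all four actors, so failure to transfer would not isolate the story. The empathy claim should not depend on that test.

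The cost is clip time-stamps, one extra split of the results, fewer rows per person and a less precise no-narrative estimate. No new data are needed.

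One limit remains and should be stated: the rating still follows both story and clip, and arousal from the story may carry over into the clip, so these steps reduce the mixing but do not remove it.
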